[13]. One way to think of this is as a fluid process, in which an experienced clinician seamlessly transitions from one decision-making model to the next, depending on the approach that seems most appropriate given the clinical context and the individual patient.

In prior work we developed a decision aid, Chest Pain Choice (CPC),
[14] and tested the hypothesis that use of the decision aid during a clinical encounter would facilitate a shared approach to medical decision-making, improve patient-centered decision-based outcomes (patient knowledge, engagement in the decision-making process and satisfaction), and safely decrease resource utilization. The decision aid described to patients the rationale for their chest pain evaluation and the potential utility of urgent cardiac stress testing. It also included a precise estimate of the 45-day risk for ACS derived from a robustly validated prediction model
[5,15,16] and communicated that risk using prose phrases, numbers, and a pictograph to account for the patient’s preferred mode of understanding numerical information
[14]. In a single-center randomized pilot trial (n = 204) we observed greater knowledge regarding management options and the short-term risk for ACS, greater engagement in the decision-making process, and a 19% lower rate of observation unit admission for cardiac stress testing in patients randomized to this shared decision-making intervention compared to usual care, and there were no major adverse cardiac events within 30 days in either arm
[11].

In this paper we describe the rationale and methods employed to test the effectiveness of the CPC decision aid in a multicenter trial in five geographically and ethnically diverse hospital EDs in the United States. We hypothesize that use of the decision aid will significantly increase patient knowledge, engagement and satisfaction, and decrease the rate of testing that may have marginal benefit in the low-risk population with no increase in adverse events.

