**Figure 2 F2:**
[figure not shown]
**The Decision Aid.** The decision aid describes for patients the rationale for, and results of, the initial emergency department evaluation (electrocardiogram, initial cardiac troponin level) and the potential utility of additional cardiac testing. A reliable estimate of the risk of an acute coronary syndrome within 45 days, obtained from a quantitative pretest probability (QPTP) web-tool developed and tested by Kline *et al*. [5,15,16], is included. The decision aid will be individualized to the patient based on the results of the QPTP risk calculator. The risk estimate is displayed using a state-of-the-art risk communication pictograph using an ordered icon array displaying natural frequencies, and a prose description of patient risk (for example, out of every 100 patients with factors like yours, 1 had a heart attack or pre-heart attack diagnosis within 45 days, 99 did not) to account for differences in numeracy preferences between patients. The decision aid also provides explicit management options (admission with urgent cardiac stress testing, follow-up with a cardiologist or the patient’s own primary care physician within 24 to 72 hours, or have the clinician make the decision on the patient’s behalf) for the clinician and patient to consider when reaching a shared decision.

In the process of preparing for the trial it became clear that one of the participating sites (University of Pennsylvania) frequently used coronary CT angiography in chest pain patients at low-risk for ACS in lieu of cardiac stress testing. To ensure the decision aid facilitated a conversation that included options relevant to the setting in which patients are frequently considered for coronary CT angiography, a second version of the decision aid was developed for use at this site (Figure 
3).

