#### Statistical considerations

In order for the study findings to maximally impact practice and policy, they will need to be adequately powered to detect differences in outcomes of interest to each of the stakeholders (patients, clinicians, shared decision-making research experts, and healthcare payers). We will have sufficient funding to enroll 930 patients, accounting for a loss to follow-up rate as high as 5% (there was 2% lost to follow-up in our pilot trial)
[11], we anticipate having complete data on 884 patients. Table 
1 shows the anticipated power we will have to detect differences in each of the patient and stakeholder-important outcomes on completion of the trial.

**Table 1 T1:** Anticipated power to detect patient and stakeholder-important outcomes on completion of the trial

**Outcome (n = 884)**	**Usual Care***	**Decision Aid***	**Difference**	**Power**
**Patient knowledge**	44% (23.3)	60% (20.9)	16% (9.5%, 22.5%)	99%
**Patient engagement in the decision-making process (n = 221)**	7.0 (5.5)	26.3 (8.2)	19.3 (18.4, 20.2)	99%
**Decisional conflict†**	35.9 (18.9)	22.3 (21.1)	13.6 (11.0, 16.2)	99%
**Trust in the physician**	79.3 (19.9)	83.4 (19.8)	4.1 (1.5, 6.7)	86%
**Patient satisfaction with the decision made (% agree or strongly agree they are satisfied)**	69.7 (25.6)	80 (25.6)	10.3 (4.6%, 16.0%)	99%
**Safety (major adverse cardiovascular events)‡**	0%	0%	0% (−−)	78%
**Proportion of patients admitted for cardiac testing**	77%	67%	10% (4.1, 15.9)	90%
**Healthcare utilization**	8.3 (0.8)	7.0 (0.7)	1.3 (1.2, 1.4)	99%

*Estimates were determined from our completed pilot randomized trial [11].

†Lower decisional conflict scores indicate less conflict experienced by patients related to feeling uninformed.

‡Non-inferiority, one-sided test with alpha = 0.05 with a maximum difference of 5%.

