We will use standard techniques appropriate for patient-randomized trials, with each outcome compared between study arms using t-tests for continuous outcomes and chi-square tests for dichotomous outcomes. Rather than assume the intervention effect is independent of the study site where the patient is seen or of the clinician who sees them, we will assess intra-site and intra-clinician correlations. We will then stratify all tests on the study site unless the intra-clinician correlation is non-trivial, in which case we will stratify on a clinician basis. We will calculate differences and their confidence intervals using standard techniques for continuous and dichotomous data. If there are differences in baseline characteristics between the two study groups, these will be accounted for using regression models that will include an indicator for study arm. Finally, we will analyze clinician surveys using regression models with robust standard errors to account for the repeated measures on clinicians.

Descriptive analyses will be performed to describe any potential heterogeneity of treatment effect (HTE) and facilitate synthesis of subgroup results in future meta-analyses. We will conduct descriptive HTE analyses by age, gender, race/ethnicity, quantitative pre-test probability of ACS, level of education, OPTION scores, and study site. The outcomes assessed with HTE analyses will be the same as those assessed in the trial (such as knowledge, engagement, satisfaction, and healthcare utilization). We will also conduct interaction testing to determine the interaction between the decision aid and each pre-specified characteristic.

Resource use will be compared both descriptively and using multivariable models. Descriptive comparison for 30-day utilization will utilize the Wilcoxon rank-sum test to account for the skewness of the outcome measures. The multivariable models for resource utilization will be estimated using the two-part or one-part negative binomial or log gamma regression models. A two-part model will be utilized for outcomes where more than 10% of the subjects have a zero outcome measure. The covariates in the multivariable models will include factors that may not be accounted for in the randomization such as comorbidities and severity of illness. Comorbidities will be measured using the Elixhauser method, which is a commonly used measure for the acute setting

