Randomizing at the patient level increases the risk of contamination between the intervention and control arms. We have taken several steps to minimize the risk of contamination. First, the 45-day ACS risk calculator is password protected and clinicians will not be able to determine an individual patient’s risk of ACS using this instrument, or have access to the decision aid
[16]. Furthermore, in our pilot trial, we observed that when clinicians did not have access to the decision aid and patients’ 45-day risk of ACS, they reverted back to their usual practice of rapid decision-making and limited discussion with patients and were reticent to engage patients in shared decision-making. Second, only the site coordinators will have access to copies of the decision aid, and clinicians will not be provided the decision aid in the usual care arm. Third, site coordinators have been carefully trained to confirm the accuracy of each of the variables needed to generate the 45-day ACS risk estimate by review and sign-off by the treating clinician, but are instructed to keep the clinician blind to a patient’s risk unless a patient is randomized to the decision aid. Fourth, every effort will be made to obtain video and audio data of the disposition discussion in both the intervention and control arms, and we will monitor for contamination by review of these data. Finally, if contamination does occur, we anticipate it will decrease the magnitude of differences observed in the intervention and control groups, biasing the results towards the null.

There are advantages and disadvantages to using two different decision aids in the context of this trial. Having a separate decision aid (Figure 
2) for the site in which coronary CT angiography is routinely used in lieu of cardiac stress testing in low-risk chest pain patients introduces heterogeneity in the intervention. However, a key aspect of contemporary evidence-based medicine involves translating evidence into practice in a manner that is sensitive to local practice context
[30] as well as patients’ values and preferences

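### Table 1's 78% power for MACE does not follow from its own inputs (they give essentially 100%), and it hides how wide the 5-point non-inferiority margin is against a planned rate of 0%

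*Protocol article*

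**What the plan says.** The power table in Statistical considerations has a row headed "Safety (major adverse cardiovascular events". It lists 0% for usual care, 0% for the decision aid, a difference of 0% with no interval, and 78% power. The table is headed n = 884, and its planning values are attributed to the pilot. The footnote to the row reads "Non-inferiority, one-sided test with alpha = 0.05 with a maximum difference of 5" (percent). No reason for 5 points is given.

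On the expected rate, the Background reports of the 204-patient pilot that "there were no major adverse cardiac events within 30 days in either arm". The Figure 2 caption gives, as a worked example of the decision aid, "out of every 100 patients with factors like yours, 1 had a heart attack or pre-heart attack diagnosis within 45 days". The Background also states the hypothesis that testing will fall without adverse events rising.

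On analysis, the text below the table has "each outcome compared between study arms using t-tests for continuous outcomes and chi-square tests for dichotomous outcomes", with differences and confidence intervals by standard techniques. It makes no exception for MACE.

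The Discussion says that contamination, if it occurs, would shrink the between-arm differences, "biasing the results towards the null".

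**The concern.** The row's rates, sample size, alpha, margin and power cannot all be right together. A power of 78% suggests a test that the intervention might well fail, one in which a pass would mean something. If true power is close to 100% because the margin is far above the planned rate, a pass says little about whether MACE has risen.

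This matters because safety is the condition on which fewer admissions would be acceptable. MACE here includes myocardial infarction and death from cardiac or unknown cause.

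The general rule for dichotomous outcomes adds to the problem. A chi-square test asks whether the arms differ. It does not test the margin in the footnote, and it cannot be computed at 0 against 0, which is the result Table 1 plans for.

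**Working it through.** **Inputs from the article.** Margin 5 points; alpha 0.05 one-sided (z = 1.645); 884 evaluable patients (930 × 0.95 = 883.5); 1:1 allocation, so 442 per arm; planning rates 0% and 0%.

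**Assumption.** The article gives no MACE rate other than 0%, so base rates of 0.5% to 2% are assumed. For context, 0 events in 204 pilot patients has a one-sided 95% upper bound of 1 − 0.05^(1/204) = 1.5%. The 1-in-100 figure in the Figure 2 caption concerns 45-day ACS, not 30-day MACE.

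**Attempt to reproduce 78%.** With a common rate p, power = Φ[0.05/SE − 1.645], where SE = √(2p(1−p)/442).

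| True rate, both arms | SE | Power |
|---|---|---|
| 0% | 0 | 100% |
| 0.5% | 0.0047 | >99.9% |
| 1% | 0.0067 | >99.9% |
| 2% | 0.0094 | 99.99% |
| 5% | 0.0147 | 96% |
| 10.6% | 0.0207 | 78% |

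For the last line, 0.05/0.0207 = 2.41, and Φ(2.41 − 1.645) is about 0.78. Exact enumeration of the score test at 442 per arm also gives more than 99.9% for rates from 0.1% to 2%.

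Other routes to 78% all leave the row's inputs:
- 221 per arm at 5% in both arms gives 77.8%.
- Two-sided-style alpha (0.025) at 442 per arm needs a rate of 8.1%.
- A continuity correction at alpha 0.05 needs 9.5%.
- At 442 per arm and rates of 0.5% to 1%, 78% corresponds to a margin of about 1.2 to 1.6 points, not 5.

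**What passes under the 5-point margin.** One-sided 95% Miettinen-Nurminen upper bounds for the risk difference, 442 per arm:
- 0 against 0 events: 0.61%
- 14 (decision aid) against 0 (usual care): 4.85%, passes
- 15 against 0: 5.12%, fails

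An uncorrected chi-square test on 14 against 0 gives a statistic of 14.2 and p of about 0.0002. The footnote's rule and the general rule would thus send opposite messages on the same data.

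**Probability that a true tripling is declared non-inferior** (score test, exact binomial enumeration):

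| Base rate → decision aid | Declared non-inferior |
|---|---|
| 0.5% → 1.5% | >99% |
| 1% → 3% | 88% |
| 1.5% → 4.5% | 49% |
| 2% → 6% | 18% |

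**Illustration of a tighter margin.** With 2 points and equal true rates, score-test power is 95%, 83%, 73% and 64% at 0.5%, 1%, 1.5% and 2%. A true 1% to 3% rise would pass about 5% of the time.

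**The case against.** MACE is a secondary outcome. Potential events are adjudicated by three blinded investigators and reported to a DSMB that can stop the trial, so the final test is not the only safety judgement. That stands, and it tempers the consequences. It does not change what the final test can claim, or make 78% correct.

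A reader might infer from the wrong power figure that the trial is underpowered for safety. The reverse is true: 78% understates the power of the stated test.

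A reader might also infer that a tripling of MACE would usually be declared safe. The documents do not support that without qualification. Tripling is undefined at the planned 0%, 1% is an assumption, and above about 1% the statement fails (49% from 1.5%, 18% from 2%).

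The footnote names a non-inferiority test for MACE and can be read as overriding the general chi-square sentence. That is a fair reading, and details of the interval may sit in a plan not shown. But the sentence covers every outcome, so one line of clarification is warranted.

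Nothing in the documents supports 2 points as the right margin. It is a debatable choice: power falls to 64% at a 2% rate, and a tripling from a very low base can still pass. Enrolment began in October 2013, so any change would come during the trial.

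The contamination remark is general and correct for the superiority outcomes, and it does not mention MACE. It is a minor point.

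**Conclusion.** The stated 78% is wrong for its row. The row's inputs give essentially 100% power, and 78% requires about 10.6% MACE in both arms, or about 5% with half the patients. Both are far from the planned 0%. This conclusion rests only on the article's own figures.

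The 5-point margin is very wide against the planned rate, since 14 events against none would pass. At base rates of about 1% or less, a non-inferiority result cannot support the claim that adverse events do not rise. That part depends on the assumed base rate and should be given as the range above. At 1.5% to 2% the test does discriminate against a tripling, failing it about half the time or more.

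The general chi-square rule does not test the margin and is undefined at the planned result. The power figure needs correcting, and the margin needs either a justification or a narrower claim.

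**What to change.** 1. Reconcile margin, assumed event rate and power in Table 1. Replace 78% with power recomputed over a stated range of rates, for example 0.5% to 2%.
2. Justify the 5-point margin, or pre-specify a tighter one agreed with the DSMB before unblinded data are seen. If neither is done, limit the conclusion to excluding a 5-point increase.
3. State that MACE is analysed by a one-sided score-based upper confidence bound (Miettinen-Nurminen or Farrington-Manning) instead of the general chi-square test. Report the bound whatever the margin, so that readers can judge it against their own threshold.
4. Minor: limit the remark on contamination to the superiority outcomes. For a non-inferiority comparison, bias towards no difference favours declaring safety.

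Cost: items 1, 3 and 4 are changes of wording and table entries, with no extra patients. A tighter margin under item 2 would be a documented change during enrolment. It lowers the stated power and makes the safety claim harder to win.

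### Meeting the 5-point MACE margin does not by itself support the hypothesis of no increase in adverse events, because the margin is out of scale with the 0% event rate planned in the same row

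*Protocol article*

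**What the plan says.** The Protocol article, Statistical considerations, plans on 884 patients with complete data. In Table 1 the MACE row gives 0% for usual care, 0% for the decision aid and 78% power. Its footnote reads "Non-inferiority, one-sided test with alpha = 0.05 with a maximum difference of 5" per cent. No reason for the margin is given. The planning rates come from the pilot, for which the Background reports that "there were no major adverse cardiac events within 30 days in either arm".

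The Background hypothesises that the aid will "decrease the rate of testing that may have marginal benefit in the low-risk population with no increase in adverse events". The row "Proportion of patients admitted for cardiac testing" expects 77% under usual care and 67% with the aid.

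The text after Table 1 plans chi-square tests for dichotomous outcomes, with differences and confidence intervals. Under Data collection, potential MACE after discharge are reported to the principal investigator and the DSMB, and the DSMB can stop the study. Under Outcome measures, blinded investigators adjudicate potential MACE. MACE is a secondary outcome; patient knowledge is primary.

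**The concern.** A non-inferiority margin states the largest increase in harm that will still be called acceptable. Here it is 5 percentage points, for an outcome planned at 0% and after a pilot with no events. If the margin lies well above any excess the trial could plausibly produce, the test will pass whether or not the aid causes harm of a size that matters. Safety is what makes a fall in admissions acceptable, so a non-inferior result could be read as support for the hypothesis when only very large increases were ruled out. The stated 78% power adds to the problem, because it suggests a test that fails fairly often.

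**Working it through.** **Inputs (all from Statistical considerations, except allocation).** 884 analysable patients, allocated 1:1 (Randomization), so 442 per arm. One-sided alpha 0.05, z = 1.645. Margin 0.05. Planned MACE 0% in each arm. Admission 77% against 67%. Usual-care MACE rates above 0% are assumptions, shown over a range.

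**The stated power.** Normal approximation: power = Φ((margin − true difference)/SE − 1.645), with SE = √[(p₁(1−p₁) + p₂(1−p₂))/442].
- 0% in both arms: no events can occur, so the test always passes and power is 100%, not 78%.
- 1% in both arms: SE = √(0.0198/442) = 0.0067; 0.05/0.0067 − 1.645 ≈ 5.8; power is about 100%.
- 10.6% in both arms: SE = √(2 × 0.106 × 0.894/442) = 0.0207; 0.05/0.0207 − 1.645 = 0.77; power = 78%.

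So 78% needs a common MACE rate near 10.6%. The reading of 442 per arm is not the cause: it gives 91.3% for the admission row (stated 90%) and 86.7% for the trust row (stated 86%). A 5% rate with 221 per arm gives 77.8%, but that contradicts both the 0% and the 884.

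**How often the test passes when risk truly rises.** Score test for the difference, summed over all binomial outcomes, 442 per arm:

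| Usual care | Decision aid | Passes the 5-point margin |
|---|---|---|
| 0% | 1% | 100% |
| 1% | 2% | 99.5% |
| 0% | 2% | 96.5% |
| 1% | 3% | 88% |
| 0% | 3% | 65% |
| 1% | 4% | 53% |
| 0% | 4% | 22% |
| 1% | 6% | about 5% |

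**Observed results that still pass.** 14 against 0 events passes (15 against 0 with a Wald interval), and so does 17 against 4. For 14 against 0 the Wald limit is 3.17 + 1.645 × 100 × √(0.0317 × 0.9683/442) = 3.17 + 1.37 = 4.5 points, below 5. Fisher's exact p for the same result is about 0.0001.

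**Scale against the expected change in care.** The net shift is 77 − 67 = 10 points, about 44 of 442 patients. A 5-point excess is 0.05 × 442 ≈ 22 events, half of those 44. This assumes that harm acts only through the net change in disposition.

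**What a smaller margin would do with the same patients.** For illustration, a 2-point margin under the score test has power of about 100% at a common rate of 0%, 99% at 0.25%, 95% at 0.5%, 83% at 1%, 73% at 1.5% and 64% at 2%. A true 2-point excess passes in 2-5% of trials (usual-care rate 0-1%), and the largest passing result with no control events is 3 against 0.

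**The case against.** The strongest reply is that the margin is not the only safeguard. A reader might infer that the trial would call the aid safe even when its own data show a clear excess. The documents do not support that. The analysis text plans a chi-square test and a confidence interval for each outcome. At 442 per arm the uncorrected chi-square p is 0.0002 for 14 against 0 and already 0.045 for 4 against 0, and the DSMB receives reports of potential MACE. The margin appears only in the footnote to a power table. This reply stands in part: a clear excess would be visible. What remains is that one result could be both significantly worse and non-inferior, and the article does not say which governs the safety conclusion.

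A reader might also infer that the test can hardly fail at all. That goes too far: it passes in 65% of trials at 0% against 3%, in 22% at 0% against 4%, and in about 5% at the margin itself, as designed. The weakness concerns excesses up to about 2 points.

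Third, it is tempting to call the margin five times the trial's own risk, because the Figure 2 caption says "out of every 100 patients with factors like yours, 1 had a heart attack or pre-heart attack diagnosis within 45 days". That is one illustration of a 45-day ACS risk in an individualised aid, not a planning rate for 30-day MACE after discharge. Only the 0% is a planning value.

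Finally, a rationale for 5 points may stand in the full protocol or analysis plan, which are not shown. That could supply the reason, but it would not change what a pass at 5 points excludes.

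**Conclusion.** The concern holds in a limited form and should be fixed. A 5-point margin is out of scale with a row that plans 0% in both arms. Meeting it does not support the hypothesis of no increase in adverse events: true excesses of 1 and 2 points pass in 99.5-100% and 88-97% of trials. These figures rest on 442 per arm, one-sided alpha 0.05, a score test and a usual-care rate of 0-1%; the article does not name the test, and a Wald interval is slightly more lenient. The 78% power does not follow from the row's inputs and should not be read as evidence of a demanding test.

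The point is not critical, because MACE is a secondary outcome and the planned confidence interval partly protects the conclusion. With no events in either arm, for example, the one-sided 95% upper limit for the difference would be about 0.6 point, which is informative whatever margin is used.

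**What to change.** 1. Before unblinded comparative MACE data are examined, the clinical investigators should either justify the 5-point margin in writing or replace it with a smaller one in scale with the expected event rate. The value is a clinical judgement; the 2-point figures above only show what 884 patients can support.
2. Replace the 78% with the power for the chosen margin, over a stated range of event rates above 0%.
3. With either margin, report the one-sided upper confidence limit of the MACE difference by a score or exact method, and limit the safety conclusion to the increase that this limit excludes. Say how the chi-square result and the non-inferiority verdict are to be read together.
4. If 5 points is kept, state that only increases of 5 points or more were tested, and do not present a pass as evidence for the hypothesis of no increase in adverse events.

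The cost is wording in the protocol and analysis plan, with no extra patients. The downside is lower stated power if events are more frequent than planned: at 2 points it falls from 83% at a 1% rate to 64% at 2%.

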#### Randomization

Patients will be randomized after informed consent is obtained and it is confirmed that all inclusion and no exclusion criteria are met, prior to the patient-clinician discussion of treatment options and patient risk. Allocation will be concealed by means of an online password-protected randomization algorithm designed using Medidata Balance™ Medidata Solutions, New York City, USA. Patients will be dynamically stratified
[19] by enrolling by site, age and sex because of the known association of age and sex with cardiovascular risk and the availability of these data at the time of enrollment. Allocation will be based on a 1:1 ratio between the intervention and usual care arms. Though we will not be able to blind patients and clinicians to use of the decision aid, we will blind the investigators and individuals not involved in providing care to the patient allocation.

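### Table 1: the 78% power for the MACE non-inferiority test does not follow from the inputs printed with it, which give essentially 100%

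*Protocol article*

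**What the plan says.** All of the planning inputs stand in the protocol article.

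- **Outcome and rates.** The Table 1 row "Safety (major adverse cardiovascular events") gives 0% under usual care, 0% with the decision aid, a 0% difference with no confidence interval, and 78% power.
- **Test.** The row's footnote reads "Non-inferiority, one-sided test with alpha = 0.05 with a maximum difference of 5" percent.
- **Source of the rates.** The table note says "Estimates were determined from our completed pilot randomized trial". The Background reports of that pilot (n = 204) that "there were no major adverse cardiac events within 30 days in either arm".
- **Sample size.** The text says "We will have sufficient funding to enroll 930 patients" and, "accounting for a loss to follow-up rate as high as 5" percent, "we anticipate having complete data on 884 patients". Table 1 is headed n = 884. One row, patient engagement, carries its own smaller n of 221; the safety row carries none.
- **Allocation.** Under Randomization: "Allocation will be based on a 1:1 ratio between the intervention and usual care arms".

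No other event rate, margin, sample size or design effect is given for the safety row.

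**The concern.** A power figure is a function of its inputs, and here the article prints all of them: rates, total n, allocation, alpha, sidedness and margin. When both true rates are zero there is no sampling variation, so the test must either always succeed or always fail. An intermediate power such as 78% is impossible at exactly 0%. The question is then whether a small non-zero rate, or another standard test, could explain it.

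The row matters because the Background hypothesises no increase in adverse events, and this row with its footnote holds the only planning figures and the only non-inferiority margin for that claim. If the row does not agree with itself, a reader cannot tell what the safety comparison was planned to show.

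**Working it through.** **Inputs.** Per-arm n = 884/2 = 442 (1:1 allocation; 930 × 0.95 = 883.5, printed as 884). Margin d = 0.05. One-sided alpha 0.05, z = 1.645. Rates 0% and 0%.

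**Does n = 884 drive the table?** Two other rows were recomputed at 442 per arm, assuming a two-sided 0.05 test.

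- Trust in the physician: difference 4.1, SD about 19.85. SE = 19.85 × √(2/442) = 1.335, and Φ(4.1/1.335 − 1.96) = 86.7%. Printed: 86%.
- Admission for cardiac testing, 77% against 67%: 91.3%. Printed: 90%.

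Both agree within 2 points, so 884 is the working sample size for these rows.

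**Safety row at the printed rate.** The only possible outcome is 0/442 against 0/442. The restricted estimates under the null are 5% and 0%, so the Farrington-Manning score statistic is

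z = −0.05 / √(0.05 × 0.95/442) = −0.05/0.01037 = −4.82.

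The one-sided 95% upper limit solves 442·d/(1 − d) = 1.645² = 2.706, so d = 2.706/(442 + 2.706) = 0.61 points. This is always below 5 points, and power is 100%. The 78% is not reproduced.

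**Safety row at non-zero common rates.** The Wald formula is power = Φ(0.05/√(2p(1 − p)/442) − 1.645). The last column is exact enumeration of the Farrington-Manning score test.

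| Common MACE rate | Wald | Score, exact |
|---|---|---|
| 0% (limit) | 100% | 100% |
| 1% | >99.99% | >99.99% |
| 2% | 99.99% | 99.9% |
| 3% | 99.7% | 99.3% |
| 5% | 96.1% | 95.3% |
| 10% | 79.8% | 79.3% |

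Solving the Wald formula for 78% gives p = 10.6%: √(2 × 0.1058 × 0.8942/442) = 0.02069, and Φ(0.05/0.02069 − 1.645) = Φ(0.77) = 78%.

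**What the pilot allows.** With 0 events in 204 patients, the one-sided 95% upper bound is 1 − 0.05^(1/204) = 1.5%. For a single arm of 102 (an even split is assumed) it is 2.9%. Power exceeds 99% over this whole range.

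**Other standard variants at 442 per arm.**

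- Null-hypothesis variance (5% against 0%): 99.9%.
- One-sided alpha 0.025 at a 2% rate: 99.96%.
- Continuity correction at a 2% rate: 99.97%.
- Superiority test of 0% against 5%: 99.8%.

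None comes near 78%.

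**Routes to about 78% that keep the 5-point margin.** A 5% rate in both arms with 221 per arm gives 77.8%. Null variance with about 110 per arm (roughly 221 in total) gives 77.7%. Both need a sample size that the row does not state.

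**The case against.** The best defence is that the literal 0% is a rounded pilot estimate and that some small positive rate was used. This fails on size: no rate near the pilot result brings power below 99%. Clustering does not help either. No design effect is stated, and at a 1% rate even a design effect of 5 leaves power at 95.5%.

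The case against making much of the error is stronger, and most of it stands. MACE is one of several secondary outcomes; knowledge is primary. Enrolment follows from funding, not from this row. On the printed inputs the error understates power, so the sample is not too small for the stated margin. The MACE definition, the 30-day window and blinded adjudication are untouched.

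Two stronger readings are tempting and should be resisted.

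- **The true margin is smaller than 5 points.** A reader might infer this because the Wald formula can be solved for 78% with smaller margins at low rates. Those solutions rest on very few expected events and do not survive an exact score test. For example, a 1-point margin at a 0.38% rate gives 78% by Wald but about 59% exactly. The 5% margin is stated once and contradicted nowhere, and a different sample size explains 78% at least as well.
- **The monitoring board is misled about safety.** The Data collection section describes the board's meetings, MACE reporting and stopping authority without tying any of it to Table 1. The article also nowhere calls the safety comparison underpowered.

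**Conclusion.** The point holds as an internal inconsistency. The stated power is 78%; the inputs printed beside it give 100%, and every standard variant tried with those inputs gives 99.9% or more. Reaching 78% at 442 per arm and a 5-point margin takes about 10.6% MACE in each arm, roughly seven times the pilot's pooled upper bound of 1.5%. At least one of the assumed rate, the sample size, the margin and the power is wrong for this row, and the article does not allow a choice between them.

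This rests on 442 per arm (half of 884) and on equal true rates in both arms, as the row's 0% difference states. It does not depend on the choice between a Wald and a score test.

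Severity is moderate. A published planning figure for the safety comparison is wrong as written, but it concerns a secondary outcome, errs towards understating power and does not affect enrolment.

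**What to change.** Make the safety row and its footnote agree, in one of two ways:

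- If the printed rates, n = 884 and the 5-point margin are what was intended, replace 78% with the power they give, about 100%.
- If 78% was computed from other inputs, print the event rate, sample size, margin and test method used. If the row rests on fewer than 884 patients, give its n in the row, as is done for patient engagement.

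In either case, name a score or exact method, because the Wald variance is zero when both rates are 0%.

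The cost is one table row and its footnote. Enrolment, data collection and follow-up do not change.
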